### Trial design

This trial will be a double-blinded, quasi-experimental study with two parallel groups. The study duration is 12 months, from January 2021 to December 2021. We will randomly assign study participants into two groups in a 1:1 allocation ratio after recruitment. After that, we will use two distinct strategies (model-based and scale-based methods) in identifying the SHIs within each group who will receive the same intervention (SD-HIVST).

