### Interventions

We will randomly allocate eligible participants to either the scale group as controls or machine learning groupas the intervention group. A statistician will identify SHIs in the intervention group using an ensemble machine learning model and using a conventional scale for identification in the control group. All identified SHIs will be eligible to participate in the SD-HIVST intervention as index participants. We define index participants as those who were consented to participate in the program.

Index participants from both groups will follow the same study procedures for SD-HIVST with monetary incentives plus peer referral. They will be required to complete a survey at the beginning of the first-time ordering and one follow-up survey three months after each time they order HIVST kits. Figure 1 is the flowchart which shows the trial procedures.

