#### The scale group/ control group

SHIs among MSM participants assigned to the empiricalscale group (hereafter, scale group) will be determined using a 6-item scale. The same scale has been used by our team in a previous study [22, 23] to measure men’s sexual health influence, with a Cronbach alpha of 0.937. The scale consists of six questions that will assess each participants’ level of contribution in spreading HIV and sexually transmitted infections (STI) related information both online and offline in the past three months. The six questions include 1) how often they talked to others about HIV and STI; 2) how much information about HIV and STI they provided to others; 3) how many people they told about HIV and STI; 4) how likely they were to ask for more information about HIV and STI; 5) who communicated more information about HIV and STI: the participants or others within their social network; 6) how often they were to ask for advice about HIV and STI. Total response scores from answering the questions range from 0 to 24. Table 1 presents a detailed summary of responses to each question.

**Table 1 Tab1:** Summarized responses of each item in the conventional scale

Typical item	Responses Categories	Method of scaling
In the past 3 months, how often did you talk to others about HIV and STI (including both online and offline)?	Never, seldom, sometimes, often, always.	5-point Likert scale, from 0 (never) to 4 (always).
In the past 3 months, how much information about HIV and STI did you provide to others (including both online and offline)?	No information provided, provided with a little information, provided with some information, provided with much information, provided with massive information.	5-point Likert scale, from 0 (no information provided) to 4 (provided with massive information).
In the past 3 months, how many people did you tell about HIV and STI (including both online and offline)?	None, few people, some people, many people, a lot of people.	5-point Likert scale, from 0 (none), 4 (a lot of people).
In the past 3 months, how likely were you to be asked for more information about HIV and STI (including both online and offline)?	Very unlikely, unlikely, neutral, likely, very likely.	5-point Likert scale, from 0 (very unlikely) to 4 (very likely).

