#### The machine learning group/ intervention group

SHIs in the intervention group will be identified using an ensemble machine learning model, which we have trained using our previous SD-HIVST intervention trial data [24]. The data from our prior SD-HIVST intervention pilot served as our training and validation data set. And the identification of the results (i.e., classification accuracy) of our proposed machine learning model outperformed the conventional scales cut-off method [22].

We determined significant predictors according to machine learning algorithms, using training dataset and validation dataset in our previous modeling study [22]. Thus, we will include questions regarding these predictors in the baseline survey. We will collect data on these selected predictors and input them into our pre-trained ensemble machine learning model. Output results from the model will show who the SHIs are in the machine learning group. If some predictor variables have unavailable or missing data, our model will still work as we can regard those data as ‘NA’ data in modeling input for prediction. Also, we trained three ensemble machine learning models in our previous modeling study for identifying SHIs. The models could distinctly predict key distributors (SHIs who are likely to distribute at least two kits to alters), key promotors (SHIs who can promote HIV testing among the first-time tested alters), and key detectors (SHIs who can contribute to positive alters detection). However, we found that the model of key distributors is also capable of identifying most of key promotors. Therefore, in this study, we will utilize the model of key distributors for SHI identification in the machine learning group as our main outcomes focus on the ability of index on motivating alters and newly-tested alters.

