### Outcomes

Our first primary outcome is to compare the average number of alters motivated by each index between two groups. The second primary outcome is to ascertain the mean number of newly-tested alters motivated by each index in each group in the same study period. Secondary outcomes will be 1) the mean number of tested alters motivated by each index in each group with HIV reactive results, and 2) evaluate the primary outcomes in subgroups categorized by age, sexual orientation, sexual intercourse history, residence, and previous HIV testing experience.

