#### Data analysis

We will use descriptive analysis to report baseline characteristics and use Shapiro-Wilk’s method for data normality test. If the data has a normal distribution, a two-sample t-test will be used to calculate a 95% confidence interval (CI) to compare the differences in outcomes between the two arms. We will use a bootstrapping method in calculating the 95% CI if the data distribution is not normal. Subgroup analysis will be used to evaluate the difference between the two groups in the different subsets of index participants. We will use R version 3.6.2 software for all the data analysis. The trial is registered with the Chinese Clinical Trial Registry (ChiCTR2000039632).

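### Subgroup differences per index participant compare men whom each arm selected by its own rule and in numbers not matched within subgroups, so they are descriptive, not randomised, contrasts

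*Protocol article*

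**What the plan says.** Under Trial design, the order of events is fixed: "We will randomly assign study participants into two groups in a 1:1 allocation ratio after recruitment", and afterwards "we will use two distinct strategies (model-based and scale-based methods) in identifying the SHIs within each group". In the scale arm, influencers "will be determined using a 6-item scale". In the machine learning arm the article says "We will collect data on these selected predictors and input them into our pre-trained ensemble machine learning model", with those predictors gathered at recruitment: "Thus, we will include questions regarding these predictors in the baseline survey".

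The Interventions section then restricts the analysed group: "We define index participants as those who were consented to participate in the program". The section on the scale group makes the number of men taken in that arm equal to the number that the model identifies, breaking ties at random. This matching applies to the arm as a whole.

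Under Outcomes, both primary outcomes are means per index, and one secondary outcome is to "evaluate the primary outcomes in subgroups categorized by age, sexual orientation, sexual intercourse history, residence, and previous HIV testing experience". Data analysis places these comparisons among index participants: "Subgroup analysis will be used to evaluate the difference between the two groups in the different subsets of index participants". The Missing data plan declares intention-to-treat, but no outcome is defined per randomised man.

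**The concern.** Overall, equal numbers are picked from two random halves of one pool. Mean alters per picked man is therefore a fair comparison of two selection strategies, leaving aside any difference in consent. Inside a subgroup the equality is lost. If the model takes few men from a subgroup and the scale takes many, the model's few are its top scorers there, and their mean tends to be higher for that reason alone. An interaction test on the same means inherits the problem.

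A reader could then conclude that a method works better in, for example, men never tested before, when it hardly selects such men and yields fewer tested alters from them. The Discussion stresses reach to marginalised men and men reluctant to test, so subgroup results are likely to attract attention.

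**Working it through.** **The plan's own figures.** The article gives no figure for the subgroup analyses. Its total of 400 index participants cannot be reproduced, because no standard deviation is printed, and nothing below rests on it. Two figures are used for scale: at least 2,000 recruits (Recruitment), so about 1,000 per arm, and 200 index participants per arm (Sample size).

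**Algebra.** In one subgroup and arm, let N be the men randomised, n the men picked and T the alters.

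- Mean per index = T/n.
- Mean per randomised man = T/N = (n/N) × (T/n).

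Randomisation makes N about equal between arms. Summed over subgroups, n is equal by design, so both measures rank the arms alike overall. Within a subgroup n may differ. With equal N, the two measures disagree in sign when the ratio of per-index means (model/scale) lies between 1 and the inverse ratio of picks (scale/model).

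**Arithmetic example (assumed figures, 200 picked per arm).**

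| | Subgroup A | Subgroup B | Total alters | Per index |
|---|---|---|---|---|
| Model | 120 × 2.0 = 240 | 80 × 0.5 = 40 | 280 | 280/200 = 1.40 |
| Scale | 40 × 2.3 = 92 | 160 × 0.6 = 96 | 188 | 188/200 = 0.94 |

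The scale is ahead per index in both subgroups, yet the model reaches more alters overall and in A.

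**Simulation 1 (all inputs assumed).** 2,000 trials; 1,000 randomised and the top 200 picked per arm; a 50:50 subgroup unrelated to yield; Poisson yield with mean exp(0.5 × latent propensity). The model score correlates 0.6 with the latent propensity and is shifted towards one level by the stated loading. The scale score correlates 0.4. Results for the level that the model disfavours, about 500 men per arm:

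| Loading | Picked, model v scale | Per-index difference | Alters, model v scale | Per randomised man | Opposite signs |
|---|---|---|---|---|---|
| 0 | equal | – | – | – | 14% (chance) |
| 0.3 SD | 79 v 100 | +0.26 | 137 v 147 | (137−147)/500 = −0.02 | 55% |
| 0.6 SD | 60 v 100 | +0.33 | 108 v 148 | (108−148)/500 = −0.08 | 87% |
| 1.2 SD | 28 v 100 | +0.51 | 55 v 147 | (55−147)/500 = −0.18 | 94% |

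Repeat runs move the percentages by one or two points. At 1.2 SD the signs also differ in 42% of runs in the favoured level. The algebra agrees: the ratio of means is (55/28)/(147/100) = 1.34, between 1 and 100/28 = 3.57.

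**Depth alone.** With both methods equally predictive (correlation 0.4 each, loading 1.2 SD), per-index differences of +0.20 in the disfavoured and −0.09 in the favoured level still appear. They reflect depth of selection only.

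**Simulation 2 (different assumptions).** Here the subgroup variable does predict yield (log rate ratio 0.5), and the model uses it while the scale does not. In the favoured subgroup the per-index means are 1.48 (model) v 1.61 (scale), while alters per randomised man are 0.436 v 0.321 and totals 218 v 160. The scale led per index while the model led on total alters in 74% of runs (54% at log rate ratio 0.3, 80% at 0.7, 8% when the model ignores the variable).

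**The case against.** **The trial asks about identified influencers, not about randomised men.** The Objectives and Hypothesis compare what influencers found by each method achieve. Each arm's subgroup mean does validly describe the yield of the men its method picks. That stands. It is a reason to keep the per-index means, but it does not make their difference a randomised effect or a ranking of the methods within a subgroup.

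**The per-randomised figure has its own artefact.** With total picks fixed, it rewards the method that spends more picks in the subgroup. Give the model no predictive skill and a 1.2 SD loading: in the favoured level it shows 195 v 147 alters, (195−147)/500 = +0.10 per randomised man. Yet it delivers about 68 fewer alters overall and is worse per index in both levels (−0.34 each). In Simulation 1 at 1.2 SD the model is ahead per index in both levels (+0.51 and +0.04) and delivers about 20 more alters overall, so its deficit in one level is partly picks moved to the other. This stands, and it rules out simply replacing one denominator with the other.

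**The predictors are not listed.** A reader might infer that the subgroup variables drive the model. The article does not say so. The recruitment survey covers sociodemographics, sexual history and testing history, which makes it plausible, and correlation of a subgroup variable with a predictor or with the scale score would be enough. The size remains unknown: disagreement in the disfavoured level is 36% at 0.2 SD and 21% at 0.1 SD, close to chance.

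**The consequence may be overstated.** A reader might also infer that subgroup results will decide where the model is deployed. The Discussion speaks of adopting the model generally, not by subgroup.

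**Conclusion.** The concern holds as a limit on interpretation. The subgroup comparison is conditioned on selection that follows randomisation and differs by arm, and nothing matches the numbers selected within a subgroup. If those numbers differ, the per-index difference mixes selection depth with selection quality.

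Reversal is a possibility whose frequency depends on assumed inputs, from chance level with no loading to 94% at 1.2 SD. It is not a prediction for this trial. It would be wrong to infer that the primary comparison is biased by this mechanism, since numbers picked are matched overall. Nor is a sign disagreement proof that the per-index result is the wrong one. The analyses affected are secondary.

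**What to change.** For each subgroup and arm, report the numbers randomised, identified and consenting. Beside the mean per index, give alters per randomised man, with men not selected counted as 0. This is the randomised contrast. Zero follows from the design, because the Discussion says that only identified influencers have access to the ordering system. Label per-index subgroup differences descriptive and draw no conclusion from them about which method works better in a subgroup.

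The cost is wording and one more table. The subgroup variables should be available for all randomised men from the recruitment survey, and Trial status says that statistical analysis has not begun. The drawback is that the per-randomised figure partly reflects how many picks each method spends in the subgroup. The two measures must be read together with the counts, and neither alone ranks the methods within a subgroup.

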## Discussion

This quasi-experimental study will evaluate the effectiveness of an ensemble machine learning model on identifying SHIs during the digital network-based secondary distribution of HIVST among MSM by comparing it with an empirical scale. Digital network-based secondary distribution leverages both social network and digital technology, and it has been proven to be feasible and can contribute to HIV testing uptake among MSM in China [25, 26]. Additionally, social network interventions for HIV prevention offer potential in the development sector, especially in this globalizing society where people are connected easily via social media and networking technology [31]. Maximizing the social network interventions by identifying the SHI might further enhance the sexual health behavior among MSM, more specifically, the distribution and uptake of HIVST. However, few studies have yet focused on it. By comparing the identification methods, we can evaluate the impact of the identified SHI, which could expand HIV testing coverage, particularly to reach the marginalized individuals or those who are reluctant to HIV and STI testing among key populations.

Nevertheless, there are a few limitations regarding ensemble machine-learning modeling and interventions that should be acknowledged. One of the limitations might be overfitting the model due to the relatively small training and testing data sets and the comparatively large prediction data set [22]. From the perspective of interventions, even if the HIVST kits are free, the setting of the deposit for each test kit may potentially impede participants from ordering and distribution, where they might have to bear the expenditure for their peers [26]. However, we believe this strategy can effectively boost the linkage to care services. In addition, due to the trial design, this HIVST ordering system is only provided to the identified SHI and limits the accessibility of all others. However, future implementation studies can resolve this by removing the restriction.

The findings of our study will have significant scientific and policy implications for the promotion of decentralized sexual health services. The study outcomes could contribute to optimizing the integrated digital network methods on HIV and STI testing. Furthermore, practical experience obtained from this implementation in real-life settings might be transferable to future initiatives to create similar self-sustaining HIV and STI testing programs among marginalized populations. If successful, similar peer-based or social network-based intervention programs can use the ensemble machine learning model for identifying the SHI to optimize outcomes.

## Trial status

We designed the study timeline to start from January 2021 to December 2021. At the time of writing this draft protocol, the recruitment process and data collection were ongoing. We will close the recruitment system on August 31, 2021, and we expect to complete all follow-ups by December 2021. Statistical analysis has not begun.

## Data Availability

Data sharing does not apply to this article as no datasets were generated or analyzed during the current study.

## Abbreviations

HIV: Human immunodeficiency virus
MSM: Men who have sex with men
SD-HIVST: Secondary distribution of HIV self-testing
SHI: Sexual health influencer
WHO: World Health Organization
SESH: Social Entrepreneurship to Spur Health
CDC: Center for Diseases Control and Prevention
Xutong: Zhuhai Xutong Voluntary Services Center
CBO: Community-based organization
STI: Sexually transmitted infection
CI: Confidence interval
